**Fig. 2 Fig2:**

Calculation of C/D ratio. In this formula, “C” represents the trough level measured in a blood sample collected immediately prior to drug dosing on the day of a trial visit (*t*_0_) and “D” denotes the daily dose taken by the patient on the day prior to the visit (*t*_-1_)

A centralised measurement of the 12-week tacrolimus blood trough level at the University Hospital Regensburg will be used to calculate C/D ratio for the primary endpoint.

During the controlled treatment phase (first 12 weeks post-randomisation), tacrolimus should be dosed by the investigator to reach and maintain whole blood trough concentrations within the general reference range of 3–12 ng/ml. For every randomised patient, a narrower target range (with an interval of 3 ng/ml) within the wider reference range of 3–12 ng/ml is to be defined at all times and continually reviewed/revised based on clinical circumstances. The first target range is to be set prospectively by the investigator and documented in the eCRF at baseline to enable analysis of the pharmacokinetic endpoints. Since the frequency of trough level measurement directly influences pharmacokinetic endpoints, each trial centre aims to follow the minimum schedule of trough level measurement outlined in Fig. 3.

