### Visit 2 to visit 6 (day 3 to day 28) of controlled treatment phase

During the first 4 weeks after randomisation, five study visits are performed and assessments should be conducted according to Fig. 4. Tacrolimus trough level measurements should be performed (at least) according to the minimum scheduled outlined in Fig. 3. A time window of ± 1 day is permitted for visits 2–4, this time window extends to ± 2 and ± 3 days for visit 5 and visit 6, respectively.

At visit 6, the patient should be assessed for signs of de novo occurrence of tremor or vision impairments. If detected, these should be documented as adverse events.

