### Sample size calculation

Sample size estimation is based on testing superiority of Envarsus® versus Advagraf™ with respect to the primary efficacy variable. C/D ratio data obtained from previously published clinical trials in kidney transplantation and observational studies in LTx inform an assumed difference between the two treatments Envarsus® or Advagraf™ after 12 weeks of approximately 0.4 with a standard deviation of 1.0.

A sample size of 100 patients per treatment group will have the power of 80% to show a difference of 0.4 in C/D ratio between the two treatment groups with a two-sided significance level of 5%. The primary test will be performed based on the Full Analysis Set (FAS) but will be repeated for the Per-protocol analysis set (PPAS). To have a sufficient power also for the PPAS comparison, it is planned to randomise 134 patients in each treatment group assuming that about 25% of randomised patients cannot be included in the PPAS because of major protocol deviations. A sample size of 134 patients per treatment group will have a 90% power to show a difference of 0.4 in C/D ratio in the FAS. The minimal detectable difference in the FAS will be 0.24.

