The recently identified C/D ratio as a cost-effective estimate for tacrolimus bioavailability will be calculated at 12 weeks after randomisation as the primary endpoint of EnGraft. Bioavailability studies on Envarsus® in the context of LTx are less prevalent in the scientific literature compared to kidney transplantation, and no prospective phase III or IV studies with Envarsus® have been conducted in de novo LTx recipients. Our aim is to show that Envarsus® confers a superior (higher) C/D ratio in LTx recipients after 12 weeks of therapy. Several studies have identified a relationship between C/D ratio and clinical outcomes in organ transplant recipients. Sánchez Fructuoso et al. demonstrated that a higher C/D ratio is linked to a reduction in neurotoxic side effects, e.g. tremor, after kidney transplantation [20]. Moreover, in 2020 von Einsiedel et al. showed in their observational study after LTx that a higher C/D ratio is associated with improved renal function, as measured by eGFR [21]. If EnGraft is able to confirm these findings and to show superiority of Envarsus® over Advagraf™ in terms of C/D ratio as hypothesised, a higher C/D ratio could improve clinical outcomes for LTx recipients and confer a real clinical benefit for Envarsus®-treated patients that will be detected by our chosen secondary endpoints.

EnGraft consists of an optional run-in phase which may last for up to 14 days after transplantation surgery. Within this period, patients may be pre-treated with an immediate-release formulation of tacrolimus (e.g. Prograf®). Tacrolimus target trough levels may be reached faster in this pre-treated subset of patients and unfairly bias the secondary endpoints that are based on drug pharmacokinetics. For this reason, “pre-treatment” was chosen as a stratification factor for the dynamic randomisation algorithm to enable a fair and unbiased evaluation of the secondary pharmacokinetic endpoints. Additionally, patients spending different amounts of time in the run-in phase prior to randomisation consequently affects the time when patients are discharged from the transplantation centres relative to the study visits. This factor may influence compliance with the minimum scheduled trough level measurements resulting in protocol deviations and potentially influencing our chosen secondary endpoints.

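### Three secondary endpoints depend on how often troughs are drawn and how long patients are followed, and a minimum schedule does not equalise either between open-label arms

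*Protocol article*

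**What the plan says.** The text under Fig. 2 in the protocol article (Objectives, Primary endpoint) states both the issue and the remedy: "Since the frequency of trough level measurement directly influences pharmacokinetic endpoints, each trial centre aims to follow the minimum schedule of trough level measurement". The section on visits 2 to 6 confirms that the schedule is a lower limit: "Tacrolimus trough level measurements should be performed (at least) according to the minimum scheduled outlined". The text shown sets no upper limit and no rule for unscheduled readings in these endpoints.

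Three entries under Selected secondary endpoints depend on the readings:
- the number of study-drug dose adjustments to week 12;
- the number of readings above and below the patient's first target range;
- the days until that range is reached, dated at the earlier of two successive in-range readings.

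The first two are numbers with no stated denominator.

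Study design says that the trial is open-label. The Fig. 2 text has the investigator dose to trough and set the target range. Under Statistical analysis, Secondary endpoints, these variables are described by arm, and any tests are optional, nominal and exploratory.

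**The concern.** The remedy does not match the problem. If frequency drives the endpoint, frequency has to be made equal or allowed for, and a floor does neither. Site staff know the arm and may order as many extra troughs as they judge necessary. Stratifying by site and by immediate-release pre-treatment balances patients at entry but does not control draws afterwards.

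Follow-up acts in the same way. A patient who dies or withdraws early has fewer readings, hence fewer chances of an out-of-range reading or a dose change, and so appears well controlled.

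At stake is the comparison of how easily each formulation is brought to target and kept there. Dose adjustments and time to the first trough target are named in the abstract among the secondary endpoints. Unequal monitoring could be reported there as a difference between formulations.

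**Working it through.** **1. The plan's own figures.** The documents give no figure for sampling frequency. The only calculation is for the primary endpoint, with an assumed difference "of approximately 0.4 with a standard deviation of 1.0".
- Patients per group for 80% power: 2 × (1.96 + 0.8416)² × 1.0² / 0.4² = 98.1, so 99. The plan says 100.
- Allowing for 25% loss from the per-protocol set: 100 / 0.75 = 133.3, so 134.
- Standard error at 134 per group: √(2/134) = 0.1222. Power: Φ(0.4/0.1222 − 1.96) = Φ(1.31) = 90.6%. The plan says 90%.
- Minimal detectable difference: 1.96 × 0.1222 = 0.239. The plan says 0.24.

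All reproduce. The week-12 C/D ratio uses a single centrally measured trough, so the number of draws does not enter this calculation.

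**2. Assumed inputs.** Fig. 3 is not shown, so the scheduled number of draws is unknown. The checks below assume 134 per arm, no drug difference, and 8 to 16 draws over 12 weeks in the less-sampled arm.

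**3. Counting artefact alone.** Let m be the mean draws (Poisson) in one arm and r·m in the other. Let each patient's out-of-range probability follow a beta(2,2) distribution, with mean 0.5 and variance 0.05. Then:
- false difference in mean count = m × (r − 1) × 0.5;
- variance of a count = 0.5m + 0.05m².

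For m = 12 and r = 1.25, the difference is 12 × 0.25 × 0.5 = 1.5 readings. The variances are 13.2 (12 draws) and 18.75 (15 draws). The standard error is √((13.2 + 18.75)/134) = 0.488, z = 3.07, and the rejection rate is Φ(3.07 − 1.96) = 87%. Simulation gave 86%.

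Simulated rejection at nominal 5%, over m = 8, 12 and 16:

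| Extra draws in one arm | False difference (readings) | Raw count | Proportion of readings |
|---|---|---|---|
| none | 0 | 4.6–5.0% | 4.9–5.3% |
| 10% | 0.4–0.8 | 22–28% | 5.2–5.4% |
| 25% | 1.0–2.0 | 79–89% | 4.7–5.4% |
| 50% | 2.0–4.0 | about 100% | 5.0–5.6% |

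A separate simulation (40% out of range on average, beta(4,6)) agrees: 24%, 69% and 95% for mean draws of 11, 12 and 13 against 10.

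**4. Readings that also change the dose.** This model assumes correlated daily troughs, a 6–9 ng/ml target range, and a dose change after every out-of-range reading. The last assumption makes dose adjustments equal the out-of-range count.

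| Draws | Mean out-of-range count | Proportion out of range | Median days to target |
|---|---|---|---|
| 10 | 5.23 | 0.523 | 14 |
| 13 | 6.50 | 0.500 | 10 |
| 16 | 7.71 | 0.482 | 7 |

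Against 10 draws, both counts differ in about 100% of trials and time in 98–100%. With equal draws the rate is 5–6%. The count worsens while time to target improves, although the drugs are identical.

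**5. Does a new definition remove it?** Not fully. In the model of step 4, the proportion is declared different in 24% of trials with 3 extra draws and 64% with 6, now in favour of the more-sampled arm. A second feedback model, also on assumed inputs (10 scheduled draws, 3 or 6 extra in the first 28 days), gave:
- proportion: 55% and 93%;
- count on scheduled readings only: 33% and 77%;
- time on scheduled readings only: 38% and 78%.

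The remainder arises because extra readings bring dose changes forward. That alters the troughs themselves, not just how they are counted.

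**The case against.** The strongest reply is that nothing in the documents shows sampling will differ by arm. A reader might take the Discussion as an admission that it will: "This factor may influence compliance with the minimum scheduled trough level measurements resulting in protocol deviations and potentially influencing our chosen secondary endpoints". It does not say that. The factor named is time spent in the run-in and its effect on discharge timing relative to study visits. The run-in precedes randomisation and should balance in expectation. This objection stands: open-label conduct permits a difference but does not establish one.

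Further points also stand. The secondary tests are optional and exploratory, and the primary endpoint does not depend on the number of draws. The troughs summarised at 1, 2, 4 and 12 weeks, and the proportions of patients below, within or above the reference range at those times, are tied to fixed times and free of the counting artefact. Every simulated rate rests on inputs that the documents do not supply. Handling of unscheduled readings and of early withdrawal may be settled in a statistical analysis plan that is not shown. Extra draws prompted by instability may also carry information about the formulation, which a scheduled-only analysis discards.

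These limit the point without removing it. The article itself fixes two bare counts and a spacing-dependent time, says that frequency influences them, and answers with a floor. Calling the tests exploratory restricts the claims that may be made. It does not remove bias from the estimates that will be reported.

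**Conclusion.** The point holds as a conditional weakness in how three secondary endpoints are defined. If draws or follow-up differ by arm, the more-sampled arm tends to look worse on the out-of-range count, worse on dose adjustments only as far as clinicians act on the readings, and faster to target. The net effect on any judgement of practicability is therefore mixed. The direct counting effect on the raw out-of-range count follows from arithmetic. The size is unknown, because the scheduled number of draws and any imbalance between arms are not given. The 22–28% rejection rate for 10% more draws is an illustration under the stated assumptions.

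A reader might infer that the practicability comparison is already biased, or that changing to a proportion cures it. The documents do not support the first, and the feedback models contradict the second. The primary endpoint and sample size are not directly affected. This is an inexpensive improvement worth making.

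**What to change.** Before database lock, settle the following for the between-arm comparison:

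- Report out-of-range readings as a proportion of each patient's readings, above and below separately.
- Report dose adjustments per week on study drug. This allows for follow-up time but not for the number of draws.
- Repeat the out-of-range and time-to-target analyses using only readings on the Fig. 3 schedule.
- Keep the raw counts from all readings as description.
- Tabulate draws per patient and follow-up time by arm.
- State that these steps remove the direct counting artefact but not the effect of extra readings prompting earlier dose changes, so any difference must be read alongside the draws per arm.

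No new data are needed. The cost is a little more analysis, and unscheduled readings are left out of one version.

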**Fig. 3 Fig3:**
[figure not shown]
Tac measurements. Minimum schedule of tacrolimus trough level measurements

C/D ratio tends to fluctuate during the first weeks and months after transplantation. Twelve weeks post-randomisation (visit 7) has therefore been chosen for timing of the primary endpoint because the overall metabolic situation in patients is expected to be stable by this time. Also, at 12 weeks, the influence of concomitant immunosuppressive agents that may affect C/D ratio should be less pronounced. Corticosteroids are often concomitantly administered with tacrolimus and are allowed as non-investigational medication products (NIMP) in the EnGraft study. Since they share some common metabolic and transporter pathways with tacrolimus, higher steroid doses and rapid steroid tapering during the early post-transplant period may interfere with tacrolimus metabolism and destabilise the C/D ratio [18, 27]. At the 12-week time point, the use of steroids should have been tapered and the C/D ratio sufficiently stable to provide an accurate estimate of tacrolimus bioavailability.

### Selected secondary endpoints

Number of IMP dose adjustments until 12 weeksTime (days) to reach the first defined range in target trough level, utilising the date of first in-range reading of two consecutive readings within the rangeNumber of measurements above and below the first defined range in target trough levelC/D ratio measured at 1, 2 and 3 yearsMean tacrolimus trough level and inter-patient variability (range) of tacrolimus trough levels at 1, 2, 4 and 12 weeksInter-patient variability (range) of tacrolimus total daily dose until 12 weeksProportion of patients with trough levels lower, within, or higher than the standard reference range at 1, 2, 4 and 12 weeksIncidence and severity (BANFF criteria) of clinically confirmed biopsy-proven rejection (BPAR) at 12 weeks and 1, 2, 3 yearsIncidence of graft failure (defined as necessity for re-transplantation) at 12 weeks and 1, 2, 3 yearsIncidence of death (for any reason) at 12 weeks and 1, 2, 3 yearsLaboratory measures of liver function, renal function and metabolism at 12 weeks and 1, 2, 3 yearsMalignancies and infections at 1, 2 and 3 yearsIncidence of de novo occurrence of tremor or vision impairmentsIncidence of post-transplant diabetes mellitus and post-transplant hyperglycaemia at 12 weeks and 1, 2, 3 years

Graft biopsies are read at each site by the local pathologist. The local assessment will be used to guide the clinical treatment of the patient during the study. A diagnosis of BPAR is based on histological grading using the BANFF criteria for hepatic allograft pathology. In addition, a central assessment of biopsy pathology will be conducted by an independent central pathologist who is blind to the treatment assignment. To avoid detection bias, the blinded central assessment will be taken as the official result for the trial and for the determination of the BPAR endpoint.

### Inclusion criteria

Patients must meet all of the following inclusion criteria to be eligible for randomisation:Signed and dated written informed consentAdult (≥ 18 years old) male or femaleRecipient of a whole liver transplant from a deceased donor or a split liver transplant from a deceased or living donorABO blood type compatible with the organ donorAble to swallow an oral formulation of tacrolimus in tablet or capsule form

### Exclusion criteria

Multi-organ transplantationAny previous organ allograft transplantationBiopsy-proven acute rejection that is ongoing at the time of randomisationOccurrence of post-transplant thrombosis, occlusion or stent placement in any major hepatic arteries, hepatic veins, portal vein or inferior vena cavaHistory of extra-hepatic malignancy that could not be curatively treatedHepatocellular carcinoma with extra-hepatic spread or macrovascular invasionUncontrolled systemic infectionRequirement of life support measures such as ventilation or vasopressor agents (> 20 μg/kg BW/h) at the time of randomisationKnown contraindication or hypersensitivity to tacrolimus, and/or to any of the excipients listed in Sect. 6.1 of the Summary of Product Characteristics (SmPC) of both Envarsus® and Advagraf™, and/or to any other macrolidesOngoing, planned or foreseeable use of cyclosporine or any tacrolimus preparation other than Envarsus® or Advagraf.™ (except for immediate-release formulations administered before randomisation)Any prolonged-release tacrolimus treatment prior to randomisationPregnant or nursing (lactating) female, where pregnancy is defined as the state of a female after conception and until the termination of gestation, confirmed by a positive hCG laboratory testFemale of child-bearing potential, defined as physiologically capable of becoming pregnant, unless using a reliable method of contraceptionParticipation in another interventional clinical trial during the time period from randomisation to study end, if the trial is testing an IMP (AMG study) or if the intervention and/or follow-up requirements of the trial impede or interfere with either the objectives of EnGraft or the treatment/follow-up requirements of EnGraftAny condition or factor which, in the judgement of the investigator, would place the subject at undue risk, invalidate communication with the investigator or study team, or hamper compliance with the trial protocol or follow-up scheduleInability to freely give informed consent (e.g. individuals under legal guardianship)

All women of childbearing potential will undergo a serum pregnancy test prior to transplantation as per site routine. Postmenopausal women (physiologic menopause defined as 12 consecutive months of amenorrhea) or women who are permanently sterilised (e.g. tubal occlusion, hysterectomy or bilateral salpingectomy) may be enrolled in the study without serum pregnancy testing.

## Interventions

### Randomisation

A dynamic allocation technique will be used for randomisation of patients fulfilling the trial eligibility criteria in a 1:1 ratio to one of two treatment arms: Envarsus® tablets (test IMP) or Advagraf™ capsules (comparator IMP). Pre-treatment with immediate-release tacrolimus (Yes/No), as well as trial site, will be used as stratification factors in the treatment allocation to minimise sources of treatment bias. The first stratification factor (study centre) will minimise systematic treatment bias at the study centre level and reduce the influence of inter-centre variability. The second stratification factor (pre-treatment with immediate-release tacrolimus) will minimise treatment bias at the level of the individual patient, since patients treated with Prograf® during the run-in phase can be expected to develop stable trough levels after randomisation more rapidly than patients who do not receive Prograf® prior to commencing IMP. Balancing the treatment arms with respect to this factor allows fair and unbiased evaluation of the secondary pharmacokinetic endpoints that evaluate the ease with which the first target trough level is achieved.

The allocation algorithm is programmed into a randomisation module in the trial database. Study investigators at the participating trial sites have access to the randomisation module via the online trial database and randomise using this central tool. It is vital that randomisation is performed as soon as possible after eligibility has been confirmed and no later than 14 days after transplantation surgery; enrolment after this time period is not allowed.

### Investigational group

Envarsus® will be supplied by the sponsor for the duration of the 12-week controlled treatment phase. Envarsus® will not be supplied for the follow-up phase (Table 1).

**Table 1 Tab1:** IMP-characteristics of Envarsus®

IMP name	Envarsus®
Active ingredient	Tacrolimus monohydrate
Pharmaceutical form	Prolonged-release tablet
Presentation	Oval, white to off-white uncoated tablet
Administration	Once daily, oral formulation provided in 0.75 mg, 1.0 mg and 4.0 mg dosage strengths

Envarsus® therapy should commence at a starting dose of 0.11–0.13 mg/kg/day.

In case the patient initially received an oral formulation of Prograf® during the run-in phase (e.g. administered via nasogastric tubing), conversion should be performed on a 1:0.7 (mg to mg) total daily dose basis. In case the patient initially received intravenous Prograf® therapy (continuous 24-h infusion) during the run-in phase at a dose approximately 1/5th of the recommended oral dose, the conversion to Envarsus® should be modified accordingly.

### Control group

Advagraf™ will not be provided by the sponsor, but supplied/prescribed as per site routine (Table 2).

**Table 2 Tab2:** IMP-characteristics of Advagraf™

IMP name	Advagraf™
Active ingredient	Tacrolimus monohydrate
Pharmaceutical form	Prolonged-release hard capsule
Presentation	Gelatin capsule with light yellow/white/orange/greyish-red capsule cap on an orange capsule body containing white powder in respectively 0.5 mg/1 mg/3 mg/5 mg dosage strengths
Administration	Once daily, oral formulation provided in 0.5 mg, 1.0 mg, 3.0 mg and 5.0 mg dosage strengths

Advagraf™ therapy should commence at a starting dose of 0.1–0.2 mg/kg/day.

In case the patient initially received an oral formulation of Prograf® during the run-in phase (e.g. administered via nasogastric tubing), conversion should be performed on a 1:1 (mg to mg) total daily dose basis. In case the patient initially received intravenous Prograf® therapy (continuous 24-h infusion) during the run-in phase at a dose approximately 1/5th of the recommended oral dose, the conversion to Advagraf™ should be modified accordingly.

